## Data safety and monitoring board

Data safety will comply with the National Statement on Ethical Conduct in Human Research. Only the responsible clinician and Chief Investigator will see identified data.

To maintain participant privacy and confidentiality, participants will not be able to use an alias/username that contains identifiable information (e.g real name, address, city you live in). If they choose an alias/username that contains identifiable information, they will be requested to change it before beginning the Program.

## Early termination

If a patient wishes to withdraw from the study once it has started, he or she can do so at any time without having to give a reason. Upon early withdrawal, all participants will be provided with encouragement to access additional services via their GP. Additionally, all participants will be given the opportunity to provide feedback about their current symptoms. If participants withdrawing from the program do report a deterioration of their symptoms, they will be contacted by the Chief Investigator to discuss access to additional services. If participants do not choose to provide feedback about their symptoms, but the investigators do have concerns about the participant’s condition, we do have consent from all participants to contact their GP. This process will be supervised by the Chief Investigator.

# Blinding and unblinding

Study is not blinded.

# STATISTICAL CONSIDERATIONS

## Sample Size Calculation

We would expect pre-post improvement of ES 1.0 for the CaCCBT groups on Anxiety Disorder measures. We also expect the CaCCBT group to improve more than the CCBT group by an ES of 0.3 and waitlist group by an ES of 0.6. Sample size is powered to have an 80% chance of detecting differences at p<.05.

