**Summary**

Protocol title: Internet Based Transdiagnostic Treatment for Anxiety - A Randomised Controlled Trial of the Anxiety Program

Protocol version: 2

Objectives Primary objective: To explore the outcomes of the Anxiety program for participants with either Generalised Anxiety Disorder (GAD), social phobia, or panic disorder (with or without agoraphobia), who receive clinician assisted computerized cognitive behavioural therapy (CaCCBT), against participants who receive computerized CBT with reminder calls from administrative staff (CCBT), against participants who remain on the wait list, using a randomized controlled trial design.

Secondary objectives: To further determine the feasibility of these treatments in terms of acceptability to patients and practicality for clinicians.

Study design: A CONSORT-R compliant, registered RCT of the intervention (CaCCBT) versus CCBT versus waitlist control group.

Planned sample size: 150

Selection criteria: Meets criteria for GAD, social phobia, or panic disorder (with or without agoraphobia) as a primary diagnosis.

Study procedure Recruit and treat subjects with GAD, social phobia or panic disorder (with or without agoraphobia)

Statistical considerations: Sample size calculation: Assuming ES > 0.5

Analysis plan: ANCOVA of post-treatment scores on measures of depression, anxiety, disability, and treatment satisfaction, while controlling for pre-treatment score. T-tests and *X*^2^ on pre-treatment scores to determine equivalence between groups.

Duration of the Study: 18 months

TABLE OF CONTENTs PAGE

1. BACKGROUND 6

1.1 Disease Background 6

1.2 Rationale for Performing the Study 7

2. STUDY OBJECTIVES 7

2.1 Primary Objective 7

2.2 Secondary objectives 8

3. STUDY DESIGN 7

3.1 Design 7

3.2 Study Groups 8

3.3 Number of Participants 8

3.4 Number of Centres 8

3.5 Duration 8

4. PARTICIPANT SELECTION 8

4.1 Inclusion Criteria 8

4.2 Exclusion Criteria 8

5. STUDY OUTLINE 9

5.1 Study Flow Chart 9

5.2 Investigation Plan 10

5.3 Study Procedure Risks 12

5.4 Recruitment and Screening 12

5.5 Informed Consent Process 12

5.6 Enrolment Procedure 12

5.7 Randomisation Procedure 12

6. SAFETY 12

6.1 Adverse Event Reporting 12

6.2 Serious Adverse Event Reporting 13

6.3 Data Safety and Monitoring Board - membership and responsibilities 13

6.4 References to national and international guidelines on research in humans 13

6.5 Early Study Termination 13

7. BLINIDING AND UNBLINDING 13

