We recently completed randomised controlled trials of clinician assisted computerised cognitive behavioural therapy (CaCCBT) for the distance treatment of people with social phobia (Titov et al, 2008a), GAD (Titov et al, 2009a), and panic disorder (Wims et al, 2008). Adherence across all the studies was good (social phobia, 80%; GAD, 75%, panic disorder 88%). Patients in the intervention groups were severe and yet made significant improvement (social phobia, ES=1.2 ; GAD, ES=1.3; Panic, ES=1.0). This level of improvement is roughly equivalent to that seen in our face-to-face anxiety disorders clinic at St Vincent’s hospital. However, the CaCCBT groups only required roughly one quarter as much clinician time as usual face to face treatment. This finding has been replicated for the social phobia program (Titov et al, 2008b), and replication studies for the GAD and depression programs will be finalised by the end of the year. Moreover, preliminary results suggest that disorder specific programs are successful in reducing symptom severity of non-targeted disorders (Titov et al, 2009b).

We have recently completed an RCT pilot study of an Internet-based treatment transdiagnostic treatment for anxiety disorders (Titov, Johnston, Robinson & Andrews, in preparation). Attendance throughout the program was roughly equivalent to that of our previous Internet-based disorder specific programs (76%), and preliminary findings support the efficacy of this initiative.

We are interested in further investigating the efficacy of Internet-based treatments for a population of people suffering from at least one of the following disorders: GAD, social phobia or panic disorder (with or without panic disorder). Additionally, we are interested in assessing the level of support required to help people complete the program as independently as possible.

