## Number of participants

150 in total: CaCCBT: n=50; CCBT: n = 50; Waitlist: n= 50

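### The unrestricted 80% power claim holds with 50 per arm for CaCCBT vs waitlist (ES 0.6) but not for the plan's own expected difference of 0.3

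*Protocol*

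**What the plan says.** Section 8.1 (Sample Size Calculation) expects the CaCCBT group to "improve more than the CCBT group by an ES of 0.3 and waitlist group by an ES of 0.6". The next sentence reads "Sample size is powered to have an 80% chance of detecting differences at p<.05". It is not limited to either comparison, and it does not say whether the test is one- or two-sided.

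Section 3.3 fixes the allocation: "150 in total: CaCCBT: n=50; CCBT: n = 50; Waitlist: n= 50". The Summary gives a shorter basis, "Sample size calculation: Assuming ES > 0.5", also without naming a comparison.

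Section 8.2 plans ANCOVA with the baseline score as covariate. No pre-post correlation is given.

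Under Primary Objectives, hypothesis 1 has both active groups improving relative to controls, so CCBT vs waitlist is a primary comparison. Hypothesis 3 predicts that the two active groups will be equivalent. No expected effect for CCBT vs waitlist is stated anywhere.

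**The concern.** The power sentence directly follows two effects that differ by a factor of two. Required sample size varies with the inverse square of the effect, so ES 0.3 needs about four times as many participants per arm as ES 0.6. One sample size can hardly give about 80% power for both.

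The interpretation of primary results is at stake. A reader told that power was 80% would take a non-significant CaCCBT vs CCBT result as support for hypothesis 3, although section 8.1 itself expects a difference of 0.3 between those arms. In the same way, a non-significant CCBT vs waitlist result would look like evidence that CCBT does not work, when the trial may simply have been too small to show an effect of that size.

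**Working it through.** **Inputs from the protocol.** n = 50 per arm (3.3); ES 0.3 and 0.6, significance level 0.05 and power 80% (8.1); ANCOVA on baseline (8.2).

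**Assumptions, because the protocol is silent.** Two-sided test as base case; ES in units of the unadjusted SD; pre-post correlation r of 0.5 to 0.7.

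**1. Trying to reproduce the stated 80%, unadjusted.** Noncentral t with 2n − 2 = 98 degrees of freedom and noncentrality d × √(n/2) = d × √25 = 5d.

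| ES | Noncentrality | Power, two-sided | Power, one-sided | n per arm for 80%, two-sided |
|---|---|---|---|---|
| 0.3 | 1.5 | 31.8% | 43.8% | 176 |
| 0.5 | 2.5 | 69.7% | 79.9% | 64 |
| 0.6 | 3.0 | 84.4% | 90.9% | 45 |

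The claim is met at 0.6 and not at 0.3. The smallest ES with 80% two-sided power is 0.57. The normal approximation gives nearly the same figures (32.3% and 85.1% at 0.3 and 0.6).

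**2. With the planned baseline adjustment.** ANCOVA reduces the residual SD by √(1 − r²), so the effective ES is d/√(1 − r²).

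| r (assumed) | Effective ES for 0.3 | Power, two-sided |
|---|---|---|
| 0.5 | 0.3/0.866 = 0.346 | 40% |
| 0.6 | 0.3/0.800 = 0.375 | 46% |
| 0.7 | 0.3/0.714 = 0.420 | 55% |

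To reach 80%, the effective ES must be 0.566, so r = √(1 − (0.3/0.566)²) ≈ 0.85. For ES 0.6 at r = 0.5 the effective ES is 0.6/0.866 = 0.693 and power is about 93%.

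**3. CCBT vs waitlist.** If both effects use the same SD, the implied difference is 0.6 − 0.3 = 0.3. The power figures for 0.3 then apply to it as well.

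**4. The Summary's ES > 0.5.** The effect of 0.6 satisfies it; 0.3 does not. At exactly 0.5, 50 per arm gives about 80% if the test is one-sided (79.9%). Two-sided with ANCOVA at r = 0.5, the effective ES is 0.5/0.866 = 0.577 and power is about 82%. So the Summary fits a comparison with waitlist at or near the 0.6 of section 8.1.

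**5. Precision.** The unadjusted 95% confidence interval for a difference has half-width 1.98 × √(2/50) = 0.40 SD. Multiplied by √(1 − r²), it is 0.34 at r = 0.5 and 0.28 at r = 0.7. Over most of that range it is wider than the expected difference of 0.3.

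**The case against.** The strongest reply is that the sentence never promises 80% for every pair of arms. It could refer to CaCCBT vs waitlist alone, where it is true, or to the three-group test. For means of 0, 0.3 and 0.6 that omnibus test has about 76% power unadjusted and about 88% with r = 0.5. This stands as a reason to call the sentence unrestricted rather than false in every reading. It does not remove the problem: the sentence follows both effects without limiting itself to one, and an omnibus rejection would not show that CCBT beats waitlist or that the active arms differ.

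Four stronger readings are tempting, and the documents do not support them.

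- A reader might infer that the Summary contradicts section 8.1 and should be deleted. But 0.6 is above 0.5, and 50 per arm is about right for 0.5 under a one-sided test or moderate baseline adjustment. The Summary lacks a named comparison; it is not wrong.
- A reader might treat the 76% in the background section as retention and recompute power with 38 per arm. That figure is programme attendance in a pilot. It is not the share giving outcome data, a waitlist has no lessons to attend, and an intention-to-treat analysis is planned.
- A reader might quote 32% as the power of the trial. It is the unadjusted figure, and the planned analysis adjusts for baseline. It would be the right figure only if the stated ES were already on the adjusted scale, which the protocol does not say.
- A reader might conclude that the trial will probably miss the 0.3 effects. At r = 0.7 the power is 55%, so that holds only for part of the plausible range.

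The 0.3 for CCBT vs waitlist is also an inference by subtraction, not a figure in the plan.

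**Conclusion.** The power statement is wrong for the plan's own ES of 0.3. Power there lies between about 32% and 55% two-sided, depending on the baseline correlation, and is 44% one-sided without adjustment. Only an unstated correlation of about 0.85 would bring it to 80% two-sided. For CaCCBT vs waitlist at 0.6 the statement is sound, at 84% or more with 50 per arm giving data.

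The result for CaCCBT vs CCBT needs only the figures in sections 3.3 and 8.1 and an ordinary range of correlations. Extending it to CCBT vs waitlist, and so to the group 2 part of hypothesis 1, also needs a common SD for the two effects. No dropout assumption is involved.

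A separate inconsistency sits beside it. Section 8.1 expects the active arms to differ by 0.3, while hypothesis 3 predicts that they are equivalent. Power to detect a difference is not the quantity that an equivalence hypothesis needs, so correcting the power figure does not settle that conflict.

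**What to change.** Keep 150 participants and restate section 8.1 by comparison, along these lines:

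> With 50 per arm and a two-sided 5% test, power for CaCCBT vs waitlist at ES 0.6 is 84% unadjusted and about 93% with baseline-adjusted ANCOVA (assumed pre-post correlation 0.5). For a difference of 0.3, that is CaCCBT vs CCBT and by implication CCBT vs waitlist, power is about 32% unadjusted and 40% to 55% adjusted (assumed correlation 0.5 to 0.7).

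Then:

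- Keep the Summary's ES > 0.5 but tie it to the comparison with waitlist that it fits.
- Report the 0.3 comparisons with 95% confidence intervals.
- State that a non-significant CaCCBT vs CCBT result is not evidence for the equivalence in hypothesis 3, and reconcile that hypothesis with the difference expected in 8.1.
- Do not enter the 76% attendance figure in the power statement as retention.

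The cost is a less favourable power statement. No extra patients are needed. The power text is a rewording, but reconciling hypothesis 3 with 8.1 requires the sponsor to decide what is being claimed about the two active arms.

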## Analysis Plan

Analyses based on completers and on intention to treat will be performed. Three mixed design ANCOVAs will be carried out utilising SPSS GLM with the baseline score entered as a covariate. The within subject factor examines the difference in pre-post scores for each of the three treatment conditions, whilst the between subjects factor compares improvement scores between treatment groups.

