# STUDY OBJECTIVES

## Primary Objectives

The primary objectives of the study is comprised of three hypotheses: 1) That participants in treatment groups 1 and 2 would show significant improvement on a general measure of anxiety (DASS-21) and on disorder specific measures (GAD-7, PSWQ, SPSQ, PDSS-SR) relative to Controls; 2) that participants in treatment groups 1 and 2 with primary diagnoses of GAD, panic, or social phobia would show significant improvement on relevant disorder specific measures (GAD-7, PSWQ, SPSQ, PDSS-SR) relative to controls with the same primary diagnoses; and 3) that treatment groups 1 and 2 will be equivalent regarding generic and diagnosis specific measures of anxiety.

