## Investigation plan

A CONSORT-R compliant, registered RCT of the intervention (CaCCBT) versus CCBT versus waitlist control group. This will demonstrate whether the benefit from the CaCCBT intervention is superior to natural remission and placebo response. Because of low adherence to CCBT we think that it is a proxy for a placebo treatment. As in any RCT accurate patient selection, good randomization, reliable and valid outcome measures, and low drop-out rates are critical. Analyses based on completers and on intention to treat will be performed.

There are already over 1000 people on the waitlist for Virtual Clinic. In addition, some media attention is expected to generate more publicity to attract people to the program. The study will be described on the intake website, [www.virtualclinic.org.au](http://www.virtualclinic.org.au). People will read the information about the studies and elect to continue or not. If they choose to apply for the study they will complete an automated screening questionnaire. Only people whose responses to the questions meet selection criteria and undergo a brief phone interview explaining the program will read the information sheet and return an electronic consent form and mail that to the investigators. This will trigger the phone interview in which the diagnosis will be confirmed using the Mini International Neuropsychiatric Interview Version 5.0.0 (Appendix A). Questions about the study will be answered and an offer of treatment made.

Patients will be randomly allocated to CaCCBT group (n=50), CCBT group (n=50), or the waitlist group (n=50). Randomization will be done via [www.random.org](http://www.random.org) (see appendix A).

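### Section 8.2 adjusts the disorder-specific scales only for their own baseline score; adding primary diagnosis, if it is recorded before the arm is known, could gain a little precision at almost no cost

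*Protocol*

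**What the plan says.** Section 8.2 describes three mixed-design ANCOVAs "utilising SPSS GLM with the baseline score entered as a covariate". The Summary repeats the choice: post-treatment scores are compared "while controlling for pre-treatment score". No other covariate is named in either place.

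Section 2.1 sets the outcomes. Hypothesis 1 compares both treatment groups with controls "on a general measure of anxiety (DASS-21) and on disorder specific measures (GAD-7, PSWQ, SPSQ, PDSS-SR) relative to Controls". Hypothesis 3 states "that treatment groups 1 and 2 will be equivalent regarding generic and diagnosis specific measures of anxiety". Neither is restricted by diagnosis. Only Hypothesis 2 uses diagnosis, by limiting the comparison to participants who "would show significant improvement on relevant disorder specific measures (GAD-7, PSWQ, SPSQ, PDSS-SR) relative to controls with the same primary diagnoses". (Scale names here follow section 2.1; sections 5.2 and 11.3 list SPSR where 2.1 has SPSQ.)

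Diagnosis is therefore collected and needed. Section 5.2 refers to "the phone interview in which the diagnosis will be confirmed using the Mini International Neuropsychiatric Interview Version 5.0.0" and describes allocation after that. Sections 5.6 and 5.7 place allocation before the brief telephone interview. Section 7 says that the trial is unblinded. Sections 5.7 and 11.4 describe a random-number list and mention no stratification.

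**The concern.** On a scale built for one disorder, participants who have that disorder are likely to score higher at entry than the others, and may also end at a different level. Adjusting for one baseline score puts all diagnoses on a common regression line. That line removes the part of the diagnosis gap that the baseline score predicts. Whatever is left stays in the error term. If the arms happen to differ in diagnostic mix, it also enters the treatment contrast.

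At stake is the width of the intervals on the disorder-specific scales, in particular for the comparison of the two active arms, where section 8.1 expects a difference of only 0.3 SD. Primary diagnosis is an entry variable that the trial needs anyway, so using it in the model would cost little.

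**Working it through.** The plan gives no figure for the value of a diagnosis term, so there is nothing of its own to reproduce on this point. From the protocol: 50 per arm (3.3), and expected differences of 0.6 against waitlist and 0.3 against CCBT (8.1). Everything else below is an assumption, because the protocol gives no diagnosis mix, between-diagnosis gap or pre-post correlation.

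**Model.** Three equally frequent diagnoses. On a given scale the target diagnosis is higher at entry by D within-diagnosis SDs. A share k of that gap remains at post-treatment. The within-diagnosis pre-post correlation is r, and within-diagnosis variance is 1 at both times. Let b = (1/3)(2/3)D² = (2/9)D².

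- Residual variance, baseline score only: 1 + k²b − (r + kb)²/(1 + b)
- Residual variance, baseline score and diagnosis: 1 − r²
- Ratio: 1 + b(k − r)² / [(1 + b)(1 − r²)]

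The ratio is never below 1. It equals 1 when D = 0 or k = r, that is, when the gap shrinks exactly along the within-diagnosis slope.

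**Example.** D = 1.5, k = 1, r = 0.5: b = 0.5, and the ratio is 1 + 0.5 × 0.25/(1.5 × 0.75) = 1.111.

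| D | k | r = 0.5 | r = 0.6 | r = 0.7 |
|---|---|---|---|---|
| 1 | 1 | 1.061 | 1.045 | 1.032 |
| 1.5 | 1 | 1.111 | 1.083 | 1.059 |
| 1.5 | 0.9 | 1.071 | 1.047 | 1.026 |
| 2 | 1 | 1.157 | 1.118 | 1.083 |
| 2 | 0.75 | 1.039 | 1.017 | 1.002 |

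The 16% is the corner D = 2, k = 1, r = 0.5.

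**A more plausible k.** Section 8.1 expects a pre-post improvement of 1.0 SD with CaCCBT, hence 1.0 − 0.3 = 0.7 with CCBT and 1.0 − 0.6 = 0.4 on waitlist, a mean of 0.7. Suppose that participants without the target disorder improve half as much on its scale (an assumption). The gap then shrinks by 0.35, so k = 1 − 0.35/D:

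- D = 1.5: k = 0.77, ratio 1.003 to 1.032 over r = 0.7 to 0.5.
- D = 2: k = 0.825, ratio 1.014 to 1.066.

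That is the basis of the 0-7%. With the two active arms only (Hypothesis 3), the mean improvement is 0.85, the gap shrinks by 0.425, and at D = 2 (k = 0.79) the ratio is 1.007 to 1.052.

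**Cost.** Residual degrees of freedom fall from 150 − 3 − 1 = 146 to 144. If diagnosis adds nothing, the standard error grows by √(146/144) = 1.007. A ratio below about 146/144 = 1.014 is thus no net gain.

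**Power.** A ratio of 1.07 is a partial R² of 1 − 1/1.07 = 0.065; 1.157 gives 0.136. At 50 per arm, two-sided 0.05, normal approximation, power = Φ(5·ES/√(1 − R²) − 1.96), taking ES in units of the residual SD before diagnosis is added:

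| Partial R² | ES 0.6 | ES 0.3 |
|---|---|---|
| 0 | 85.1% | 32.3% |
| 0.065 | 87.3% | 34.1% |
| 0.136 | 89.8% | 36.5% |

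**Chance imbalance.** The SD of the between-arm difference in the share with one diagnosis is √(2 × (1/3)(2/3)/50) = 0.094. The diagnosis gap that baseline adjustment leaves is D(k − r)/(1 + b). At D = 1.5, k = 1, r = 0.5 this is 0.5, so a 2-SD imbalance (0.189) moves the contrast by 0.09 SD. At D = 2, k = 0.825, r = 0.5 the remaining gap is 0.34 and the shift 0.06 SD.

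**The case against.** Adjusting for the outcome's own baseline is valid and standard. Further covariates are often left to a statistical analysis plan, and section 8.2 does not say that the list is closed. That lowers the weight of the point but does not remove it: the protocol states its covariate in two places, and a stated choice can be improved.

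The own-scale baseline already carries much of the diagnosis information, and the gain vanishes when k is near r. This stands, and it is why the range starts at zero and 16% should not be quoted as the expected gain.

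Three stronger readings are tempting, and the documents do not support them:

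- *That the comparison is biased.* Allocation is random, so omitting diagnosis costs precision only. Chance imbalance is already part of the standard error.
- *That the earlier results by disorder prove the need.* Section 1.1 reports "social phobia, ES=1.2 ; GAD, ES=1.3; Panic, ES=1.0", but these come from separate disorder-specific programs. They do not show that diagnosis predicts the post-treatment score beyond baseline in this program.
- *That every whole-sample model loses precision and diagnosis is simply there to be used.* The DASS-21 is a general measure, for which D is presumably near 0. Section 8.2 does not map its three ANCOVAs to hypotheses, so their use for Hypotheses 1 and 3 is an inference. And under sections 5.6-5.7 the diagnosis may be made after allocation in an unblinded trial. Adjusting for a diagnosis that knowledge of the arm could influence might itself introduce bias.

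**Conclusion.** The point holds as a modest efficiency improvement for the disorder-specific scales. Without diagnosis their residual variance is 0-16% larger over the assumed range, more plausibly 0-7%. This rests on equal diagnosis frequencies, D up to 2, r of 0.5-0.7 and one k common to all arms, none of which the protocol supplies. In power, a 7% gain is worth about 2 percentage points at either expected difference.

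No conclusion about the design changes. A reader might hope that the added term rescues the comparison of the two active arms, but at a difference of 0.3 power stays below 40% with or without it. That shortfall is a separate matter.

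**What to change.** 1. Reconcile section 5.2 with sections 5.6-5.7, so that it is clear whether the diagnostic interview or the allocation comes first.
2. In section 8.2, and in the Summary to match, prespecify primary diagnosis (GAD, social phobia, panic disorder) as a three-level factor beside the baseline score in the whole-sample models for the disorder-specific scales. Say which hypothesis each model serves. The DASS-21 model does not need the term.
3. State that the factor is the diagnosis recorded before the arm is known. If the interview follows allocation, use the classification from pre-allocation screening instead.

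The cost is one model term, 2 degrees of freedom and a sentence or two of text. No new data are needed if diagnosis precedes allocation. Otherwise the screening step must record a primary disorder for each applicant, which the protocol does not now say it does.

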# Study OUTLINE

## Study Flow Chart

Enrolment (Feb 2010-March 2010)

Randomisation

Pre-treatment “Pre-treatment” assessment

assessment (April) time point (April)

CaCCBT and CCBT Waitlist control

Treatment Phase (10 weeks including “mid treatment

(10 weeks including mid assessment” time point)

treatment assessment)

Post-treatment assessment Pre-treatment assessment (begin

(June) active treatment, June)

Treatment Phase(10 weeks)

3 month follow up (September) Post-treatment assessment (August)

Writeup (2011)

##

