**Lesson Eight:**

- **Revise the skills you have learnt.**
- **Make a plan for staying well in the future.**

Participants in the CaCCBT group will receive regular email contact with their clinician, and will be encouraged to carry out homework activities.The patients in the CCBT groups will have same access to the lessons, and homework activities as the CaCCBT groups. Unlike the CaCCBT groups, the CCBT groups will have no clinician contact over the 10 week period, but will receive weekly telephone reminders from administrative staff. The waitlist group will not receive any treatment during this period.

After the treatment group has finished the program, all participants will complete a third set of diagnostic questionnaires. The waitlist group, and any CCBT participants wishing to complete the program with clinician contact, will be offered additional treatment after this.

Effectiveness of the CaCCBT program for anxiety will be measured by comparing waitlist and CCCBT and CaCCBT groups on their pre- and post- treatment scores. Long-term follow up data will compare the CaCCBT and CCBT groups at 3 month follow up.

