## Study Procedure risks

In applying to join the program, patients with severe depression/suicidality will be screened out and encouraged to see their GP. Patients will need to meet inclusion/exclusion criteria before joining the study. After satisfying these criteria, patients will be measured at pre-treatment, mid-treatment, post-treatment time points, with CaCCBT and CCBT groups measured at 3 month follow up and the waitlist control group measured immediately after completing the active treatment phase. If any responses to questionnaires at any of these timepoints indicate deterioration in wellbeing, this will be raised with the Chief Investigator, and or clinician to determine the best way of dealing with these difficulties. Additionally, regular team meetings (at least 3 times a week) will be conducted to monitor any difficulties patients may be having and ways of best dealing with these difficulties. Adverse events will be monitored by the investigators and reported to the Ethics Committees.

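### Mid-treatment scores are scheduled in all three arms but enter no stated efficacy analysis, leaving the completer pre-post ANCOVA open to bias if drop-out depends on early response and differs between arms

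*Protocol*

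**What the plan says.** Schedule. Section 5.3 states that "patients will be measured at pre-treatment, mid-treatment, post-treatment time points", and then gives the extra later assessments for the treated arms and the waitlist separately. The flow chart in 5.1 puts a mid-treatment assessment inside the 10-week phase for CaCCBT and CCBT, and a matching time point in the waitlist column. Section 5.2 says that after treatment "all participants will complete a third set of diagnostic questionnaires", which fits pre, mid and post as sets one, two and three.

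Analysis. Section 8.2 reads "Three mixed design ANCOVAs will be carried out utilising SPSS GLM with the baseline score entered as a covariate" and continues "The within subject factor examines the difference in pre-post scores for each of the three treatment conditions". The Summary plans "ANCOVA of post-treatment scores on measures of depression, anxiety, disability, and treatment satisfaction, while controlling for pre-treatment score". Section 5.2 measures effectiveness by comparing "groups on their pre- and post- treatment scores". None of the three places mentions the mid-treatment score.

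The only stated use of interim responses is monitoring in 5.3: "If any responses to questionnaires at any of these timepoints indicate deterioration in wellbeing, this will be raised with the Chief Investigator". Sections 5.2 and 8.2 also promise both a completer and an intention-to-treat analysis, without saying how a missing post score is handled in the latter.

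**The concern.** For someone who stops between the mid and post assessments, the mid score is likely to be the best available predictor of the missing post score. A pre-post GLM makes no use of it. If those who stop are mainly people doing badly at mid-treatment, the remaining completers look better than the arm as randomised. If this happens more in one arm than in another, the contrast between them shifts.

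Unequal loss is foreseeable here. Section 5.2 expects adherence to CCBT to be low enough to treat that arm as a stand-in for placebo, while CaCCBT has clinician contact. Two primary hypotheses are exposed: superiority of each treated arm over waitlist, and equivalence of the two treated arms (2.1). Extra selective loss from CCBT would flatter CCBT and shrink the observed CaCCBT-CCBT difference, towards the equivalence that the third hypothesis states.

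This is separate from how baseline enters the model. A plain ANCOVA of post on pre leaves out the same data.

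**Working it through.** The plan gives no figure for missing post scores or for this bias, so there is nothing of its own to reproduce. The size below is illustrative.

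**Inputs from the protocol**
- 50 per arm (3.3).
- CaCCBT better than waitlist by 0.6 and than CCBT by 0.3 (8.1), which implies CCBT better than waitlist by 0.6 − 0.3 = 0.3.
- Pilot attendance 76% and earlier adherence 75% to 88% (1.1). As a proxy for missing questionnaires these give losses of 24%, and of 12% to 25%.

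**Assumptions not in the protocol**
- SD 1 at each visit; correlations pre-mid 0.6, pre-post 0.5, mid-post 0.7.
- Post scores missing: 24% CaCCBT, 40% CCBT, 10% waitlist.
- 50% to 80% of losses fall after the mid assessment. In the treated arms the odds of late loss rise 2.7-fold per SD worse mid score. Earlier losses and waitlist losses are unrelated to score.

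**Estimators**, on simulated arms of at least 400,000, so that the results show bias and not chance:
- Completer: regress post on arm and pre among those with a post score.
- With mid: within each arm, regress mid on pre, and post on pre and mid; then average the predicted post score over everyone randomised. This is the maximum-likelihood estimate when loss depends only on observed scores.

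**Results** (50% and 80% late loss)

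| Contrast | True | Completer pre-post | With mid |
|---|---|---|---|
| CaCCBT vs waitlist | 0.60 | 0.65, 0.67 | 0.60 |
| CCBT vs waitlist | 0.30 | 0.39, 0.42 | 0.30 |
| CaCCBT vs CCBT | 0.30 | 0.26, 0.25 | 0.30 |

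The third row agrees with the first two: 0.65 − 0.39 = 0.26 and 0.67 − 0.42 = 0.25. The bias against waitlist is 0.05 to 0.07 SD for CaCCBT (0.05/0.60 = 8%; 0.07/0.60 = 12%). The CaCCBT-CCBT difference shrinks by 0.04 to 0.05 SD. If only the CCBT loss were selective, it would read 0.18 to 0.21.

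**Set against sampling error.** Completers would number 50 × 0.76 = 38 and 50 × 0.60 = 30. The standard error of the CaCCBT-CCBT contrast is √[(1 − 0.5²)(1/38 + 1/30)] = √(0.75 × 0.0596) ≈ 0.21. A shift of 0.05 is 0.05/0.21 ≈ 0.24 standard errors.

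**A different drop-out model.** Let all loss follow the mid assessment and depend on pre-to-mid change (log-odds slope 1 to 2 per SD), with 5% unselective loss in the comparator and half the effect present at mid. For a true 0.60:

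| Situation | Estimate |
|---|---|
| Completer, 12% selective loss in active arm | 0.65 to 0.68 |
| Completer, 25% selective loss in active arm | 0.70 to 0.75 |
| Completer, equal 25% selective loss in both arms (slope 1) | 0.595 (0.597 with no loss) |
| Completer, 25% loss unrelated to response | 0.60 |
| Completer, 25% loss of good early responders (slope −1) | 0.50 |
| All randomised, mid score carried forward, 12% to 25% selective loss | 0.47 to 0.55 |
| All randomised, baseline carried forward, same loss | 0.56 to 0.63 |
| Mid score used in a likelihood-type analysis | 0.60 |

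With a true effect of zero and selective loss in the active arm, the completer analysis gives 0.05 to 0.15 and baseline carried forward gives 0.07 to 0.16.

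**The case against.** The strongest reply is that 8.2 also promises an intention-to-treat analysis. Run in GLM, it needs some value for each missing post score, and that value could come from the mid score, by carrying it forward or by multiple imputation. A separate analysis plan may hold the rule, so its absence here is no fault. This stands. A reader might infer that the whole plan overstates any arm whose poor early responders stop. The document does not support that: carrying the mid score forward leans the other way at the planned effect, and equal selective loss leaves the contrast almost unbiased.

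Second, the size rests on assumptions. Lesson attendance is not questionnaire return, and the 40% CCBT loss appears nowhere in the protocol. This also stands. It limits the figures, not the mechanism.

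Third, a reader might infer that the bias would decide the equivalence hypothesis. It would not under these inputs: both treated arms lose people, the biases partly cancel, and the shift is about a quarter of a standard error.

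Fourth, the content of the mid-treatment set is not itemised. Section 5.2 describes the questionnaires as given pre and post, section 1.2 matches control measurement to those two points, and the third set could be counted from screening. The scheduling of a mid-treatment assessment is clear from 5.1 and 5.3; which primary scales it contains is not.

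Finally, the mid assessment may exist for safety monitoring, and a protocol need not model every such visit. That is fair, but it does not make the stated model the better choice when the data are already being collected.

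**Conclusion.** The point holds in a limited form. Mid-treatment assessments are scheduled in all three arms, and no stated efficacy analysis uses them. Section 8.2 positively fixes a pre-post GLM, so this questions a stated choice and is not a complaint about missing detail. The completer analysis is biased when drop-out both depends on early response and differs between arms. Under the assumed correlations and loss rates the bias is 0.05 to 0.07 SD on a true 0.60 against waitlist, and a shrinkage of 0.04 to 0.05 SD on a true 0.30 between the treated arms. It vanishes if loss is unrelated to response, largely cancels if selective loss is equal, and reverses if good responders leave. No direction can be stated for the intention-to-treat analysis from this document. The case for change is that a better method is available from data already scheduled, at little cost; the plan is not invalid without it.

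**What to change.** In 8.2, make the intention-to-treat analysis of each primary scale a likelihood-based repeated-measures model, for example SPSS MIXED:
- outcomes: mid and post scores;
- covariate: baseline score, with a baseline-by-time term;
- factors: arm, time and arm-by-time;
- covariance: unstructured;
- arm contrasts read at the post-treatment time point.

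Keep the completer ANCOVA as a sensitivity analysis. Apply the model to the primary scales already in the mid-treatment set, and list in the protocol which these are. Adding an absent scale is optional and brings a small participant burden.

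Cost: new wording in 8.2, a different SPSS procedure and slightly more analysis work, with no new patients or visits. The model removes the bias only if drop-out depends on observed scores alone. Participants lost before the mid assessment still contribute no outcome, so for them it rests on baseline and arm only. The gain in precision is small, about 2% to 8% of the sampling variance under the first set of assumptions, so protection against bias is the main reason to change.
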